To account for the fact that individuals within a cluster, here a GP practice, might be more similar to each other than to individuals in other clusters, the number of participants required for an individually randomized trial has to be increased. The sample size calculations were adjusted for cluster randomization using the variance inflation factor (VIF) [27]. We allowed for variation in practice size and adjusted the sample size calculations for three groups of practices recruiting either 50–60, 61–74 and 75–100 patients. Allowing for intra-cluster correlation of 0.025, an overall coefficient of variation of 0.2, and mean cluster sizes of 55, 68 and 88 the VIF was estimated as 2.4, 2.7 and 3.3 respectively. Multiplying the VIF with the sample size estimated for individual randomization for each stratum, we would need a total of 8488^1^ patients. If we are recruiting three groups of 40 practices with 50–60, 61–74, or 75–100 patients each, then 120 practices will result in approximately 90% power. Assuming 50% uptake, this would result in 2122 patients having the Cytosponge™ test. If the uptake is lower, the overall number of patients entered into BEST3 will be increased so that still a total of 2122 patients will have the Cytosponge test.

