**Secondary endpoints (all to be estimated together with (nominal) 95% Confidence Intervals):**
To estimate the diagnostic accuracy of the Cytosponge™ in primary care the sensitivity will be calculated as the proportion of TFF3 positive tests in patients with endoscopy confirmed BE (gold standard). The specificity will be calculated as the proportion of TFF3 negative tests in endoscopy confirmed BE negative patients amongst the 10% participants randomly invited to endoscopy from TFF3 negative patients.To confirm the prevalence and incidence of BE and cancer stage diagnosis in the intervention and control arms for 10 years: Long term follow up data will allow Cox proportional hazard model analysis to compare oesophageal cancer and death rates.The acceptability of both Cytosponge™ and endoscopy tests will be assessed as the proportion of patients willing to have the test among patients offered the test. 95% confidence intervals (Clopper-Pearson) will be used.

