Firstly, to obtain sufficient power without greatly expanding the number of participants and practices required, we plan the addition of an individually randomised group to the current design. Practices already setup or trained to take part in the cluster-randomised arm will be permitted to continue with this randomisation method. Newly engaged practices will randomise using individual randomisation methods. The sample size calculations have also been updated to include patients in the intervention arm with a false-negative Cytosponge™-TFF3 test as having the same chance of a BE diagnosis via routine endoscopy as in the control arm (10%). This adjustment and the updated uptake of the Cytosponge™-TFF3 test allowed us to estimate that about 1.4% patients in the intervention arm will be diagnosed with BE within 1 year of follow-up. Requiring 90% power and a significance level of 0.05% gives am updated sample size of 6764 individually randomised patients. The VIF for practices randomised up to now is 3.72, whereas we are using a VIF of 4.5 for practices which have not been randomised yet as we do not know the number of recruited patients yet. One individually randomised participant would therefore be equivalent to 3.72 or 4.5 cluster randomised participants. Based on confirmed and projected numbers of participants in cluster-randomised practices, we anticipate 11,816 patients from 100 practices contributing the equivalent of 2924 individually randomised patients. That would leave 3840 to be recruited from practices employing individual randomisation and a total sample size of 15,656 participants overall.

Secondly, due to small numbers of smaller practices, stratification by both area and practice size has resulted in imbalances in arm allocations for some areas. Stratification by practice size will not be taken into account during randomisation anymore, but in the analysis instead.

These changes will ensure that the sample size will be sufficiently large to detect differences in BE diagnosis between the two arms and that the study will be completed in the time frame required.

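### Plain Clopper-Pearson intervals for Cytosponge and endoscopy uptake ignore clustering by practice and will be too narrow if uptake varies between practices; by how much depends on an uptake ICC that the protocol does not give

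*Protocol article*

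**What the plan says.** The Secondary endpoints paragraph under Statistical analysis defines the acceptability of both Cytosponge and endoscopy as a proportion, "assessed as the proportion of patients willing to have the test among patients offered the test", and then fixes the interval: "95% confidence intervals (Clopper-Pearson) will be used". Its heading describes all the secondary estimates as "all to be estimated together with (nominal) 95% Confidence Intervals". Nothing there mentions practice.

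Elsewhere the plan treats practice as a source of correlation:

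- **Sample size calculations** accepts that "individuals within a cluster, here a GP practice, might be more similar to each other than to individuals in other clusters". It sets the inputs as "Allowing for intra-cluster correlation of 0.025, an overall coefficient of variation of 0.2, and mean cluster sizes of 55, 68 and 88", with the result that "the VIF was estimated as 2.4, 2.7 and 3.3 respectively".
- **Pilot phase and 6-month milestone review** updates this: "The VIF for practices randomised up to now is 3.72, whereas we are using a VIF of 4.5" for practices still to be randomised.
- **Primary endpoint** includes cluster in the model, and Table 7 makes the amended primary analysis a stratified test that carries the variance inflation.

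The invitation to the Cytosponge test is a letter from the patient's own GP team (Patient invitation to BEST3 intervention). Patients for the research endoscopy are drawn at random within practice databases (Invitation for research endoscopies).

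**The concern.** Clopper-Pearson is exact for a binomial count, that is, for independent patients with a common probability. Here the letter, its sender and the reminder come through the practice, so acceptance can plausibly vary from one practice to another. This also applies where patients are individually randomised, because they too are nested in practices. Any positive ICC makes the binomial variance too small and the interval too short.

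Uptake matters in this trial. Willingness to have the test is a listed endpoint, Table 2 also compares it with acceptance of endoscopy, and low uptake caused the redesign after the milestone review. The Economic evaluation section updates the uptake parameter in the cost-effectiveness model and plans value-of-information analyses, which depend on how uncertain each parameter is. If the uncertainty in uptake were taken from this interval, it would be understated.

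**Working it through.** **Inputs from the protocol article**

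- ICC 0.025, coefficient of variation (CV) 0.2, mean cluster sizes 55, 68 and 88 (Sample size calculations). All were set for BE diagnosis.
- Cluster-randomised part after the milestone review: 11,816 patients in 100 practices, worth 2,924 individually randomised patients. Variance inflation factors (VIFs) are 3.72 and 4.5.
- Cytosponge uptake 27% (Table 7).
- Research endoscopy invitation: 10% of those without an endoscopy during the study.

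**Step 1: reproduce the plan's VIFs.** VIF = 1 + ((1 + CV²) × m − 1) × ICC.

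- m = 55: 1 + (1.04 × 55 − 1) × 0.025 = 2.405 (plan 2.4)
- m = 68: 2.743 (plan 2.7)
- m = 88: 3.263 (plan 3.3)
- Cluster-randomised part: the plan's figures imply 11,816 / 2,924 = 4.04. The formula at m = 11,816 / 100 = 118.16 gives 4.05.

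So a VIF of about 4 is the plan's own figure, but for BE diagnosis.

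**Step 2: Cytosponge uptake, if its ICC were also 0.025.** Patients offered the test in cluster-randomised intervention practices: 11,816 / 2 = 5,908. Acceptances at 27%: 1,595.

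- Plain Clopper-Pearson on 1,595 of 5,908: 25.9% to 28.1%, width 2.28 points. (The upper limit is 28.15%, so it may round to 28.2%.)
- Clopper-Pearson at 27% on n / VIF:

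| VIF | Effective n | Interval | Width (points) | Plain width / correct width | Real coverage of the plain interval |
|---|---|---|---|---|---|
| 3.72 | 1,588 | 24.8% to 29.3% | 4.43 | 0.52 | 69% |
| 4.04 | 1,462 | 24.7% to 29.4% | 4.62 | 0.49 | 67% |
| 4.5 | 1,313 | 24.6% to 29.5% | 4.88 | 0.47 | 64% |

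Coverage = 2Φ(1.96 / √VIF) − 1.

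**Step 3: range over the unknown uptake ICC.** Same VIF formula with CV 0.2. The width ratio is approximated by 1 / √VIF. The ICC values are assumptions.

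| Assumed uptake ICC | Cytosponge, m = 118.16: VIF | Ratio | Coverage | Endoscopy, m = 11.8: VIF | Ratio |
|---|---|---|---|---|---|
| 0.005 | 1.61 | 0.79 | 88% | 1.06 | 0.97 |
| 0.01 | 2.22 | 0.67 | 81% | 1.11 | 0.95 |
| 0.025 | 4.05 | 0.50 | 67% | 1.28 | 0.88 |
| 0.05 | 7.09 | 0.38 | 54% | 1.56 | 0.80 |
| 0.10 | 13.19 | 0.28 | 41% | 2.13 | 0.69 |

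The endoscopy cluster size is 10% of 118, about 12 per practice. This is an upper figure, since patients already endoscoped are left out.

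**What cannot be computed.** The remaining 3,840 patients come from practices that randomise individuals. Their number per practice is not stated, so no VIF can be given for them.

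**The case against.** - **The VIF of about 4 was not set for uptake.** This stands. Both the ICC and the VIFs serve the BE-diagnosis sample size. A reader might infer that the plan itself sizes clustering of uptake at 4, so that the intervals will be half the correct width. The documents support that only as a conditional statement.
- **The same sentence covers endoscopy uptake, where the effect is small.** This stands. At ICC 0.025 the plain endoscopy interval has about 0.88 to 0.89 of the correct width, depending on whether the CV is included. The Cytosponge-versus-endoscopy comparison therefore does not simply inherit a factor of two, and no interval method is stated for it.
- **Cytosponge clinics serve several practices.** This stands, by the Cytosponge clinic procedure section. The argument for clustering rests on invitations and reminders, not on clinics. That uptake is clustered is plausible but not shown.
- **Applying VIF 4.05 to all 7,828 intervention patients** (half of 15,656). A reader might do this, but the figure of 118 per practice holds only for the cluster-randomised part.
- **Harm downstream.** The Economic evaluation section says that uptake will be updated in the model. It does not say that this interval is the input, and the budget-impact description does not name uptake.
- **Detail of this kind belongs to the statistical analysis plan.** This does not stand here, because the protocol names a specific method and that method assumes independence. Calling the intervals nominal makes no allowance for clustering.

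**Conclusion.** The point holds in a limited form. The protocol fixes an interval that assumes independent patients for two uptake proportions gathered practice by practice. With any positive uptake ICC, the stated 95% limits are too narrow. The point estimates do not change.

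If uptake had the ICC assumed for BE diagnosis, the understatement for Cytosponge in the cluster-randomised practices would be serious in relative terms (a factor of about two in width) and modest in absolute terms (roughly one percentage point at each end). For endoscopy it would be minor. A smaller or larger uptake ICC moves this either way, as the range above shows. These figures rest on 27% uptake, an even split of the 11,816 patients and a mean of 118 per practice.

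This concerns the precision of descriptive secondary endpoints. It does not touch the primary comparison, which takes clustering into account.

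**What to change.** For the Cytosponge and endoscopy uptake proportions, replace the plain Clopper-Pearson interval with one that takes practice as the cluster. Either of these would do:

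- Clopper-Pearson on the sample size divided by the estimated design effect; or
- an intercept-only logit GEE with robust standard errors at practice level.

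Estimate the clustering from the uptake data, separately for the two tests, and do not carry over the ICC of 0.025. Include the individually randomising practices as clusters too.

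The change is a sentence of wording. It needs only the numbers invited and accepting per practice, no new patients and no change of design. The cost is wider intervals.

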### Economic evaluation

#### Primary endpoint

To gain an in-depth understanding of the health economics of the Cytosponge™-TFF3 test we will undertake a detailed analysis of the cost and cost-effectiveness of the Cytosponge™-TFF3 test versus usual care from the perspective of the NHS and personal social services. For the cost analysis, cost components will include costs of diagnosis using the Cytosponge™-TFF3 test, endoscopies and biopsies, endotherapy, oesophagectomy, and follow-up in primary and secondary care. Volume of resource use data will be collected from practice records up until 12 months after study entry. Unit costs will be taken from published sources such as NHS Reference Costs, the British National Formulary, and the Personal and Social Services Research Unit (PSSRU). We will calculate mean (SD) and median (IQR) costs for both study arms for each cost component and all components combined.

Cost-effectiveness will be measured in terms of the incremental cost per QALY gained. We will adapt a previously-developed decision analytic model which compared the cost-effectiveness of three strategies: Cytosponge™ screening with confirmatory endoscopy, endoscopy alone, and no screening, for 50 year-old men with GERD. The parameters for prevalence of BE, sensitivity and specificity of screening, uptake of the Cytosponge-TFF3 test, costs and utilities will be updated to reflect the BEST3 data. For these and all other parameters, including disease progression and management strategies, we will search the literature for updated evidence. We will extend the modelled population to also include women over 60 years, obtaining gender/age-specific parameters from BEST3 or searches of the literature where necessary. We will also undertake value-of-information (VoI) analyses, based on the notion that investing in further research on probabilities of events, HRQL and costs will reduce decision uncertainty about the cost-effectiveness of the Cytosponge-TFF3 test. This will include both the expected value of perfect information (EVPI) and the expected value of partial perfect information (EVPPI). The latter focusing on individual model parameters or groups of parameters.

As well as looking at total costs, costs will be disaggregated by sector since this may affect implementation of the Cytosponge™-TFF3 test. Using epidemiological data on the national incidence of reflux predominant symptoms plus cost data from the present study we will also undertake a budget impact study to calculate what the total cost would be to the NHS if the Cytosponge™-TFF3 test was rolled out nationally.

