### Objectives

Primary and secondary objectives, and endpoints are summarised in Table 2 and described below.

**Table 2 Tab2:** BEST3 Trial objectives and endpoints

Objective	Endpoint	Usual care arm	Intervention arm
Primary objectives			
1. To compare histologically confirmed BE diagnosis between intervention and control	BE diagnosis within 12 months of joining the study (excluding BE found on random 12 month research endoscopy that will occur following 12 month snapshot).	Anonymised data aggregated by sex and age group from: - GP databases - Confirmed by upper GI endoscopy (biopsy result) as recorded in the GP record within 12 months	Anonymised data aggregated by sex and age group from: - GP databases - Confirmed by upper GI endoscopy (biopsy result) as recorded in the GP record within 12 months In addition, for patients with Cytosponge™ -TFF3 test: - Endoscopy record and pathology results
Secondary objectives			
(i) To evaluate the cost of the Cytosponge™-TFF3 test versus usual care Objective (ii) To evaluate the cost-effectiveness of the Cytosponge™-TFF3 test versus usual care	(i) Mean cost per patient receiving the Cytosponge™-TFF3 test versus usual care. Costs to include costs of diagnosis using the Cytosponge™-TFF3 test, endoscopies and biopsies, endotherapy, oesophagectomy, medications, and follow-up in primary and secondary care. (ii) Incremental cost per QALY gained of the Cytosponge™-TFF3 test versus usual care	(i) Volume of resource use (endoscopies and biopsies, endotherapy, oesophagectomy, medications, and follow-up in primary and secondary care) from patient records. Unit costs (of each item of resource use) from published sources. (ii) Calculation of incremental cost per QALY gained to be based on a pre-existing model, supplemented with new data from the Trial.	(i) Volume of resource use (Cytosponges™, endoscopies and biopsies, endotherapy, oesophagectomy, medications, and follow-up in primary and secondary care) from patient records. Unit costs (of each item of resource use) from published sources. (ii) Calculation of incremental cost per QALY gained to be based on a pre-existing model, supplemented with new data from the trial.

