### BEST3 intervention: Cytosponge™-TFF3 test

#### Patient invitation to BEST3 intervention

All participants in the intervention arm, who have not opted out of the study, will receive a second letter from their GP team inviting them to have the Cytosponge™-TFF3 test. This communication will include a standalone Cytosponge™ information leaflet (Additional file 1: Figure S1). This leaflet was developed based on findings from a qualitative study on the acceptability of the Cytosponge™ test [19] followed by several rounds of review by patient and public involvement (PPI) representatives. Once a participant has expressed interest by returning a reply slip or telephone call, the participant will receive a telephone call to further assess eligibility based on a short questionnaire. If eligible, an appointment will be arranged. The participant will then be sent a Cytosponge™ patient information sheet, consent form and appointment confirmation.

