### Pilot phase and 6-month milestone review

The study design described here is the original design submitted in the first version of the protocol for Health Research Authority approval including ethical review. This protocol was used for the pilot phase of BEST3, which consisted of the first 6 practices, to evaluate the feasibility of this design. The study design was then amended based on the findings from the these practices (uptake = ~ 30%; male: female ratio = 46:54%) (Table 6). In brief, patients will receive one reminder about their invitation to make a Cytosponge™-TFF3 test appointment. Furthermore, we may adopt a shorter follow up period for practices recruited later in the trial using a simulation tool to ensure parity across datasets. This will allow timely completion of the trial. Overall, the pilot phase showed that the study design was logistically sound and that the full study could go ahead.

**Table 6 Tab6:** Amendments to the study protocol post pilot phase

Pilot study findings	Amendments to study protocol
Female to male ratio slightly higher than 50:50 overall	If the proportion of females to males consistently exceeds 55:45 within the overall cohort, the study team may institute a 50:50 split for females: males in line with known BE prevalence, at the discretion of the Trial Statistician.
Cytosponge™ appointment uptake < 50%	Patients will receive a total of one reminder in the form of a letter, phone call or text message.
Time required for practice and patient recruitment might take longer for each practice than anticipated	Practices recruited in the latter stages of the trial may adopt a 6 month follow-up period to allow timely completion of study activities with a simulation tool used to ensure parity across the datasets.

Due to the continuing low uptake of less than 30% further amendments were made after the 6-month milestone review (Table 7).

**Table 7 Tab7:** Amendments to the study protocol post 6 months milestone review

Milestone review findings	Amendments to study protocol	Details

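### The trial tests the offer of the Cytosponge, but the stated cost components and the Table 2 cost endpoint describe the test, so invitation, reminder, eligibility-call and missed-appointment costs are not named

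*Protocol article*

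**What the plan says.** Under Economic evaluation, the protocol article states that "cost components will include costs of diagnosis using the Cytosponge™-TFF3 test, endoscopies and biopsies, endotherapy, oesophagectomy, and follow-up in primary and secondary care". On volumes it says "Volume of resource use data will be collected from practice records up until 12 months after study entry", and on the summary, "We will calculate mean (SD) and median (IQR) costs for both study arms".

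Table 2 gives the intervention-arm data source as "Volume of resource use (Cytosponges™, endoscopies and biopsies, endotherapy, oesophagectomy, medications, and follow-up in primary and secondary care) from patient records". It defines the cost endpoint as "Mean cost per patient receiving the Cytosponge™-TFF3 test versus usual care".

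The section on patient invitation describes what is delivered: "All participants in the intervention arm, who have not opted out of the study, will receive a second letter from their GP team". That letter offers the test and encloses a leaflet. For those who express interest, "the participant will receive a telephone call to further assess eligibility based on a short questionnaire"; if eligible, they are booked and sent an information sheet, consent form and appointment confirmation. Table 6 adds, after the pilot, "Patients will receive a total of one reminder in the form of a letter, phone call or text message".

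Cost and cost-effectiveness are named as the main secondary objectives. The trial costs update the cost-per-QALY model and feed a national budget impact study.

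**The concern.** The primary objective and analysis concern the offer: all patients entered are compared by arm, whether tested or not. The detection gain is therefore that of an invitation programme. Both cost lists start at the test and run through later care, and Table 2 attaches the cost to patients who receive the test. A programme that invites many people to test a few also spends money on those it does not test. Usual care has no Cytosponge invitation, reminder or eligibility call, so leaving these items out can only favour the intervention. The cost comparison, the cost per QALY and the estimate of national roll-out cost would all be affected.

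The two denominators also conflict. A mean over tested patients leaves out most of the arm and sets a self-selected minority against the whole usual-care arm. A mean over the arm keeps the randomised comparison.

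**Working it through.** **1. Items of the offer against the cost plan**

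| Item | Who receives it | Named in either cost list? |
|---|---|---|
| Invitation letter and leaflet | All intervention-arm patients who have not opted out | No |
| Reminder (Table 6) | Invited patients | No |
| Eligibility call, booking | Responders only | No |
| Missed appointments | Booked patients who do not attend | No |
| Database search (Randomisation section) | Every consenting practice, before randomisation | No; not an intervention-only cost |
| Cytosponge test | Tested patients | Yes |

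**2. Reproducing the plan's figure at 27% uptake**

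Inputs: uptake 27% (Table 7); sensitivity 85%, prevalence 4% and usual-care diagnosis rate 0.6% (Sample size calculations); false negatives diagnosed at the usual-care rate (Table 7).

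Intervention rate = 0.27 × 0.85 × 0.04 + 0.73 × 0.006 + 0.27 × 0.15 × 0.006 = 0.00918 + 0.00438 + 0.000243 = 0.013803, the plan's figure of about 1.4%.

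Comparing 0.6% with 1.3803% at 90% power and two-sided 5%, without continuity correction, gives 3,382 per arm and 6,764 in total. This is exactly the stated sample size, so the uptake and rates used below are the plan's own.

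**3. Invitations per test and per extra diagnosis**

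- Invitations per test = 1/uptake: 1/0.27 = 3.70, against 1/0.50 = 2.0 as first planned. Ratio 3.70/2.0 = 1.85.
- Extra diagnoses per invitee = 0.013803 − 0.006 = 0.007803. Invitations per extra diagnosis = 1/0.007803 = 128; tests per extra diagnosis = 0.27 × 128 = 35.
- At 5% prevalence, the upper end of the stated 4–5%, the rate is 0.016098 and invitations per extra diagnosis are 1/0.010098 = 99.

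**4. What an assumed unit cost would imply**

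Let c be the cost of invitation and reminder per invitee. No value for c is given; these are assumptions.

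| c (£, assumed) | Per tested patient, c/0.27 | Per extra diagnosis, c/0.007803 |
|---|---|---|
| 1 | 3.7 | 128 |
| 5 | 18.5 | 641 |
| 10 | 37.0 | 1,282 |

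As a share of total cost per tested patient, (c/0.27)/(T + c/0.27), with all other cost T also assumed:

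- T = £100: 3.6%, 15.6% and 27.0% for c = 1, 5 and 10.
- T = £200: 1.8%, 8.5% and 15.6%.

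**5. Per patient in the arm**

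Here the omission is about c per invited patient whatever the uptake. Only the reminder added after the pilot raises it. The eligibility call adds its own cost times the proportion who respond, which the article does not give.

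**The case against.** The strongest reply is that a condensed article has not decided to leave these costs out. The word include does not close the list: Table 2 has medications, which the economic section omits. The cost of diagnosis with the test is not itemised and could contain invitation and booking. Line-item costing often sits in a fuller document, and the wording of the Table 2 endpoint may be loose shorthand for the arm. All of this stands as far as it goes: the offer costs are neither named nor excluded.

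A reader might infer more than the documents support:

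- That the offer is costed at zero because the Table 4 extract has no field for letters or calls. Table 4 has no field for the Cytosponge either, yet Table 2 costs it. Table 2 also records the number of patients invited, so volumes exist.
- That search, letter, reminder and call are all spent on everyone offered the test. The call reaches only responders, and the search is run in both arms before randomisation.
- That the shortfall grew because uptake fell. This is true per tested patient but not per patient in the arm.
- That a definite sum is missing. Any such sum rests wholly on assumed unit costs.

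The reply does not dispose of the denominator conflict, which is in the text, or of the fact that both lists and the Table 2 source follow the test rather than the offer being evaluated.

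**Conclusion.** The point holds in conditional form: if the lists and the Table 2 endpoint are followed as written, the cost of the strategy would be understated, and only in the intervention's favour. It is more than missing detail, because Table 2 and the economic section specify different denominators for a main secondary objective, and the Table 2 version leaves out the roughly 73% who are offered the test but not tested.

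The monetary size is unknown. The firm quantities are 3.7 invitations per test and about 128 per extra diagnosis (99 at 5% prevalence), resting on the plan's own uptake, sensitivity, prevalence and usual-care rate. They ignore opt-outs, who receive no invitation, and they cover invitation and reminder only. No effect on cost per QALY can be shown from the document. The primary clinical comparison is not affected. The plan should be corrected before the economic analysis.

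**What to change.** In Table 2 and the economic evaluation section:

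- Add a cost component for the offer: invitation and reminder for all invited intervention-arm patients, eligibility call and booking for responders only, and missed appointments.
- Take volumes from the trial's invitation and booking counts rather than from patient records, and apply postage and staff-time unit costs.
- Define the cost endpoint as mean cost per patient in each randomised arm, with cost per tested patient as a supplement.
- Carry the component into the cost-per-QALY model and the budget impact.
- Count the practice database search only in the roll-out and budget impact costing, since it is run in both arms of the trial.

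If a fuller economic plan already counts these items, a sentence saying so and one agreed denominator would be enough. The price is a little extra costing work, with the number invited already recorded, and slightly less favourable cost figures.
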